## Abstract

**Background:**

Breast cancer survivors suffer physical impairment after oncology treatment. This impairment reduces quality of life (QoL) and increase the prevalence of handicaps associated to unhealthy lifestyle (for example, decreased aerobic capacity and strength, weight gain, and fatigue). Recent work has shown that exercise adapted to individual characteristics of patients is related to improved overall and disease-free survival. Nowadays, technological support using telerehabilitation systems is a promising strategy with great advantage of a quick and efficient contact with the health professional. It is not known the role of telerehabilitation through therapeutic exercise as a support tool to implement an active lifestyle which has been shown as an effective resource to improve fitness and reduce musculoskeletal disorders of these women.

**Methods / Design:**

This study will use a two-arm, assessor blinded, parallel randomized controlled trial design. People will be eligible if: their diagnosis is of stages I, II, or IIIA breast cancer; they are without chronic disease or orthopedic issues that would interfere with ability to participate in a physical activity program; they had access to the Internet and basic knowledge of computer use or living with a relative who has this knowledge; they had completed adjuvant therapy except for hormone therapy and not have a history of cancer recurrence; and they have an interest in improving lifestyle. Participants will be randomized into e-CUIDATE or usual care groups. E-CUIDATE give participants access to a range of contents: planning exercise arranged in series with breathing exercises, mobility, strength, and stretching. All of these exercises will be assigned to women in the telerehabilitation group according to perceived needs. The control group will be asked to maintain their usual routine. Study endpoints will be assessed after 8 weeks (immediate effects) and after 6 months. The primary outcome will be QoL measured by The European Organization for Research and Treatment of Cancer Quality of Life Questionnaire Core 30 version 3.0 and breast module called The European Organization for Research and Treatment of Cancer Breast Cancer-Specific Quality of Life questionnaire. The secondary outcomes: pain (algometry, Visual Analogue Scale, Brief Pain Inventory short form); body composition; physical measurement (abdominal test, handgrip strength, back muscle strength, and multiple sit-to-stand test); cardiorespiratory fitness (International Fitness Scale, 6-minute walk test, International Physical Activity Questionnaire-Short Form); fatigue (Piper Fatigue Scale and Borg Fatigue Scale); anxiety and depression (Hospital Anxiety and Depression Scale); cognitive function (Trail Making Test and Auditory Consonant Trigram); accelerometry; lymphedema; and anthropometric perimeters.

**Discussion:**

This study investigates the feasibility and effectiveness of a telerehabilitation system during adjuvant treatment of patients with breast cancer. If this treatment option is effective, telehealth systems could offer a choice of supportive care to cancer patients during the survivorship phase.

**Trial registration:**

ClinicalTrials.gov Identifier: NCT01801527

## Background

Approximately 4.4 million women worldwide live with a diagnosis of breast cancer [1]. Developments in screening and improved treatments for breast cancer have led to improved survival [2,3]. Cancer is increasingly viewed as a chronic disease and therefore there is a growing need for long-term treatments [4,5]. Breast cancer survivors suffer physical impairment after oncology treatment [6,7]. This impairment reduces quality of life (QoL) and increases the prevalence of conditions associated with an unhealthy lifestyle (for example, decreased aerobic capacity and strength, weight gain, and fatigue) [8]. The reduction of range of movement in the neck/shoulder complex and chronic pain in the neck/shoulder complex are the most prevalent musculoskeletal dysfunction associated with oncology treatment [9,10].

There is evidence that physical activity is effective in the primary and secondary prevention of chronic diseases [11]. There is increasing evidence that patients with cancers such as breast, colon, prostate cancer, and hematological malignancies may benefit from physical exercise programs in terms of improvement in fitness levels, physical activity, and health-related quality of life (HRQoL) [4]. In fact, many previous studies, such as observational studies [12] and randomized controlled trials [13], have assessed the effects of physical activity on treatment-related symptoms and recovery outcomes. For this reason, physical activity has become an aim of cancer recovery research for breast cancer patients [14].

One of common postoperative complications is reduced range of motion (ROM) in the shoulders of breast cancer patients [15-17]. Much research has supported performing early exercises to avoid limitations of ROM in the shoulder [15,18]. This and other impairments may improve with physical activity in women with breast cancer [19] therefore adequate measurements should be implemented to improve disability in breast cancer women.

Recent work has shown that exercise programs after diagnosis of breast cancer adapted to individual characteristics of patients are related to improved overall and disease-free survival [1]. The benefits of regular physical activity as a way of recovery show enough scientific evidence to justify the development of new health services that respond to the needs of these patients after cancer process. However, the implementation of this type of program involves high cost resources that usually are not viable and require that participants live near the facilities which is not possible in non-urban women or women of low socioeconomic status [20].

Nowadays, technological support is a promising strategy that could improve issues such as barriers of distance, time, and cost [21]. Patients have the great advantage of quick and efficient contact with the health professional. On the other hand, the health professional can provide therapeutic intervention more efficiently in response to a patient’s needs. The monitoring of some variables (for example, weight, heart rate, and arm mobility) allows the control of these patients, which may provide improved adhesion of programs that seek to increase the QoL of these patients. The motivation of patients can be increased significantly using the telehealth system by immediate feedback that may be responsible for an active approach to fitness.

A systematic review [22] supports the view that telerehabilitation can lead to similar clinical outcomes compared to traditional rehabilitation programs, with possible positive impact on some areas of healthcare utilization. There are internet-based programs that increase amount of physical activity in different types of diseases such as multiple sclerosis [23] and juvenile idiopathic arthritis [11]. In particular, recent research [24] reported a home-based exercise program that has shown to effectively improve affected upper-limb symptoms (for example, lymphedema) and led to improved QoL of breast cancer patients. The role of telerehabilitation through therapeutic exercise is not known as a support tool to implement an active lifestyle which has been shown as an effective resource to improve fitness and reduce musculoskeletal disorders in these women [25].

It is relevant to the future of patients in a clinical setting to know whether a telerehabilitation intervention to improve physical status and reduce pain shows benefits compared to usual care in breast cancer survivors.

## Methods

### Objectives

The overall objective of the e-CUIDATE telerehabilitation randomized controlled trial is to evaluate the immediate and long-term effects of a telerehabilitation program on the overall impact of QoL, pain, body composition, physical measurement, cardiorespiratory fitness, fatigue, anxiety and depression, cognitive function, and lymphedema. The intervention group will receive three training sessions each week for an 8-week period. We will also study the effect of a 24-week period without telehealth support on the studied variables.We hypothesize that a strategy for care based on telerehabilitation to promote therapeutic exercise will increase QoL, reduce musculoskeletal disorders, and improve fitness in breast cancer patients.

### Research design and methods

A randomized controlled trial will be conducted with assessments at baseline, 4 weeks and immediately after intervention (at 8 weeks). Follow-up measurements will be carried out 24 weeks after the end of the 8-week intervention period, giving a total trial data collection period of 32 weeks. The assessments will be performed on 2 separate days to avoid fatigue in the patients. The study assessment schedule is shown in Table 1.

**Table 1 T1:** Study assessment schedule

**Assessment**	**Baseline**	**Follow****-****up**	**Post****-****intervention**	**Detraining**
		**(4 weeks)**	**(8 weeks)**	**(24 weeks)**
Informed consent	X			
*Day 1 testing*				
Sociodemographic data	X			
Anthropometric data, pressure/rate heart	X		X	X
Training on the treadmill	X			
Lymphedema	X		X	X
*Day 2 testing*				
Piper Fatigue Scale-revised	X	X	X	X
Trail Making Test	X		X	X
Auditory Consonant Trigram	X		X	X
EORTC QLQ-C30	X	X	X	X
EORTC QLQ-BR23	X	X	X	X
International Fitness Scale	X		X	X
Brief Pain Inventory short form	X	X	X	X
Hospital Anxiety and Depression Scale	X		X	X
Visual Analogue Scale for pain	X		X	X
Algometry	X		X	X
Body composition	X		X	X
Handgrip strength	X		X	X
Back muscle strength	X		X	X
Multiple sit-to-stand test	X		X	X
Abdominal test	X		X	X
6-min walk test	X		X	X
Borg Fatigue Scale	X		X	X
Accelerometry (1 week)	X		X	X
*Questionnaire to be completed at home after accelerometry*				
Questionnaire	X		X	X
IPAQ-SF Satisfaction survey			X	

### Specific research aims

1. To investigate the effects of telerehabilitation-based controlled exercise and adapt the needs of this population on physical fitness and pain perceived parameters.

2. To assess characteristics of breast cancer survivors more adequate to receive benefits from interactive program of telerehabilitation.

### Participants

A total of 80 breast cancer survivors will be randomized to receive the interactive rehabilitation or usual care. The telerehabilitation group will receive an 8-week interactive intervention and the control group will receive printed material at the beginning of the study. Breast cancer survivors will be recruited through the services of the oncology and breast unit at the Virgen de las Nieves Hospital and San Cecilio Hospital in the province of Granada. This study has been approved by the Medical Ethics Committee of the University of Granada and the local Ethical Boards of the participating hospitals.

### Eligibility criteria

To be eligible for this study participants will need to meet the following criteria: diagnosis of stage I, II, or IIIA breast cancer; medical clearance of participation; free of chronic disease or orthopedic issues that would interfere with ability to participate in a physical activity program; access to the Internet; basic ability to use a computer or living with someone who has this ability; completion of adjuvant therapy except for hormone therapy; no history of cancer recurrence; have interest in improving lifestyle: fitness/stress level; have signed informed consent.

### Assessment

#### Primary outcome measure

##### Quality of life

*The European Organization for Research and Treatment of Cancer Quality of Life Questionnaire Core 30* (EORTC QLQ-C30) *version 3*.*0*[26]: QoL will be assessed using EORTC QLQ-C30. This is one of the most widely-used instruments for measuring QoL in cancer patients. The questionnaire includes both multi-item scales and single-item measures. These are composed by five functional scales, three symptom scales, a global health status/QoL scale, and six single items; the scores have to be averaged and transformed linearly to obtain a range of score from 0 to 100 with higher score meaning a great response level [27].

*The European Organization for Research and Treatment of Cancer Breast Cancer*-*Specific Quality of Life questionnaire* (EORTC QLQ-BR23) [26]: It is a breast cancer module of EORTC QLQ-C30. This module contains 23 items assessing disease symptoms, side effects of treatment, body image, sexual functioning, and future perspective. All items are rated on a four-point scale ranging from 1 (not at all) to 4 (very much). The scoring procedure of the breast cancer module is the same as the EORTC QLQ-C30 [27]. The reliability has been found high to moderate (Cronbach´s α ranged between 0.46-0.94) [28].

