### Sample size

The estimated sample size was determined for the primary outcome variable, that is, overall HRQoL using EORTC QLQ-C30 version 3.0 [26]. According to previously reported data [57] a minimally important difference of this HRQoL instrument is 5 to 10 points. Assuming that telerehabilitation increase HRQoL in breast cancer survivors respect control group we can detect differences of at least 5% with a power of 90% and an α of 0.05 with two groups (telerehabilitation and usual care group) of 36 participants assuming similar standard deviation of approximately 7 points. We will assume a maximum loss at follow-up of 10% [58]. We will recruit a total of 80 breast cancer survivors (that is, one intervention group and one usual care group of 40 persons each). Figure 1 shows the flow diagram of the study participants.

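### The primary outcome is two whole questionnaires in the abstract and outcome section but one QLQ-C30 score in the sample size section, with no primary time point named

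*Protocol article*

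**What the plan says.** The protocol article describes the primary outcome in three places.

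- **Abstract, Methods / Design.** "The primary outcome will be QoL measured by The European Organization for Research and Treatment of Cancer Quality of Life Questionnaire Core 30", continuing "version 3.0 and breast module called The European Organization for Research and Treatment of Cancer Breast Cancer-Specific Quality of Life questionnaire". No scale is named. On timing: "Study endpoints will be assessed after 8 weeks (immediate effects) and after 6 months".
- **Assessment, Primary outcome measure, Quality of life.** Both questionnaires stand under this heading. Of the QLQ-C30 scales and items it says: "These are composed by five functional scales, three symptom scales, a global health status/QoL scale, and six single items". Of the QLQ-BR23 it says: "This module contains 23 items assessing disease symptoms, side effects of treatment, body image, sexual functioning, and future perspective". The number of QLQ-BR23 scores is not given, and nothing says that the scores are combined.
- **Sample size.** The calculation is for the "primary outcome variable, that is, overall HRQoL using EORTC QLQ-C30 version 3.0". The QLQ-BR23 is not mentioned. The claim is that "we can detect differences of at least 5% with a power of 90% and an α of 0.05 with two groups" of 36 each, with a standard deviation of about 7 points.

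The Data analysis section applies ANCOVA to the study variables in general and refers to group by time effects. It names no primary score or visit. Table 1 also collects both questionnaires at 4 weeks.

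**The concern.** Which score at which time decides the trial is a protocol-level decision, and here the protocol gives two incompatible answers. Under the sample size definition there is one variable, and alpha 0.05 is spent on it. Under the other definition there are at least 15 scores, plus an unstated number from the breast module, and the power statement covers only one of them. Even the single-variable version leaves a gap: the label in the Sample size section is not a scale name in the Quality of life section. The nearest is global health status/QoL, but the reader has to infer that.

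If this stays open until the data are seen, a reader of the results cannot tell whether a reported primary finding was prespecified or picked out of many. The nominal 5% error rate could then not be relied on.

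**Working it through.** **1. The plan's own sample size.** Inputs from the Sample size section: difference 5 (written as a percentage, read here as points on the 0 to 100 scale), SD 7, power 90%, alpha 0.05 with sidedness not stated, 10% loss.

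n per arm = 2 (z_alpha + z_power)² SD² / difference²

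- Two-sided: 2 × (1.960 + 1.282)² × 49/25 = 41.2, so 42 per arm.
- One-sided: 2 × (1.645 + 1.282)² × 49/25 = 33.6, so 34 per arm.
- Loss to follow-up: 36 / 0.90 = 40 per arm, 80 in total, as stated.

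The stated 36 is close to the one-sided result and short of the two-sided one. Power at 36 per arm is 91.7% one-sided and 85.8% two-sided. That is a separate matter. What counts here is that the calculation is for one comparison of one score.

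**2. Number of candidate scores.** QLQ-C30: 5 + 3 + 1 + 6 = 15. QLQ-BR23: five content areas are named. Assuming at least one score each gives 15 + 5 = 20 or more.

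**3. Conditional false-positive chance.** Two assumptions that the article does not make: any one score with p < 0.05 (two-sided) would count as the primary result, and there is no true effect on any score. For k independent tests the chance of at least one is 1 − 0.95^k. For correlated tests it was simulated with 200,000 draws of equally correlated null z-statistics. The article gives no correlation, so a range is shown.

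| Case | Independent | Correlation 0.5 | Correlation 0.7 |
|---|---|---|---|
| 15 scores, one time | 53.7% | 36.0% | 25.6% |
| 20 scores, one time | 64.2% | 41.9% | 29.0% |
| 20 scores, one time, only results favouring the intervention | 39.7% | 21.0% | 14.5% |

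With 20 scores at two times (40 tests) the figure is 1 − 0.95^40 = 87.1% if all are independent. With an assumed correlation of 0.5 between times it is 63.4% at between-scale correlation 0.5 and 46.6% at 0.7. A single group by time test per score would bring the count back towards the one-time rows.

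**4. Under the sample size definition.** One score at one time: 5%. One score tested unadjusted at both times: 1 − 0.95² = 9.75% if independent, 9.0% at correlation 0.5.

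**5. What keeping everything primary would cost.** Bonferroni over 20 scores tests each at 0.05/20 = 0.0025. With difference 5 and SD 7 assumed for every score, two-sided power per score at 36 per arm is about 50%, and 90% power needs 73 per arm. For just two primary scores (0.025 each), power is 78.5% and 90% needs 49 per arm.

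**The case against.** The strongest reply is that the Sample size section is the only place that defines a primary variable, that the Quality of life section merely describes instruments, and that the mismatch is therefore one of labelling. Part of this stands: the Sample size section is the natural anchor for a fix. But the abstract states outright that the primary outcome includes the breast module, so a reader must overrule one section to follow another.

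Several stronger readings are tempting and are not supported.

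- A reader might infer that a positive primary result would arise by chance about half the time. That needs a rule that any one score suffices, and a correlation between scales. The article gives neither, and the answer moves from 5% to well over half depending on what is assumed.
- A reader might infer that the trial has no error control. A multiplicity rule may sit in the full protocol or an analysis plan that is not shown, so its absence from an article is not a defect in itself. An unseen plan cannot, however, agree with both definitions.
- ANCOVA on all study variables might be read as making them all primary. It describes one method used for every outcome.
- The lower end of the reliability range quoted for the QLQ-BR23 (0.46) might be read as ruling it out as primary. The figure comes from a cited source, is not tied to a particular scale, and has no bearing on this point.

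**Conclusion.** The point holds as an inconsistency that must be resolved. Two sections make both whole questionnaires primary, a third makes one QLQ-C30 score primary under a label that matches no listed scale, and two endpoint times are given without a primary one. The stated alpha of 0.05 and power of 90% can apply only to the sample size definition.

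Confidence is high for the contradiction. The size is conditional. If any of about 20 scores could count at two-sided 5%, the false-positive chance at one time is roughly 29% to 64%, or 15% to 40% for results favouring the intervention. This rests on at least 5 QLQ-BR23 scores and on between-scale correlations from 0.7 down to 0. If the single score governs, it is 5%, or 9% to 10% over two unadjusted times.

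**What to change.** Bring the abstract and the Primary outcome measure section into line with the Sample size section:

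- Name one primary score by its scale name. QLQ-C30 global health status/QoL is the nearest match to the variable used for the sample size.
- Name one primary time point. Week 8, the end of the intervention, is one option. The Objectives give immediate and long-term effects equal standing, so the sponsor should confirm the choice.
- Test that score at that time at 5%, and say so in the Data analysis section.
- Make all other QLQ-C30 scales, the whole QLQ-BR23 and the remaining visits secondary, reported with confidence intervals.

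The Trial status section says that recruitment is active, so the choice should be recorded before outcomes are analysed.

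The cost is a change of wording. This change adds no participants, visits or questionnaires, and all data are still reported. The downside is that the QLQ-BR23, the other scales and the other visits lose the primary label. If the sponsor wants to keep more than one primary score, alpha has to be divided and the sample size recalculated, as step 5 of the working shows.

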### Other outcome measures

#### Pain

Algometry is used to measure pressure pain threshold (PPT) [29] levels through an electronic algometer (Somedic AB, Farsta, Sweden). We assess bilaterally PPTs over the C5-C6 zygapophyseal joint, deltoid muscle, and tibialis anterior muscle. The order of assessment for the different points was randomized between participants. The pressure is at an approximate rate applied of 30 kPa/s by a 1 cm^2^ probe. We ask for participants to press the switch when they first feel a change from pressure to pain. The mean of three tests (intra-examiner reliability) is used for the main analysis. There is an interval delay of 30 s between each test [30]. The reliability of pressure algometry has been found to be high the same day (intraclass correlation coefficient=0.91 (95% confidence interval (CI) 0.82-0.97)) [31] and between 4 separate days (intraclass correlation coefficient=0.94-0.97) [32].

The Visual Analogue Scale (VAS) is a scale for subjective pain estimation that consists of scores in the range of 0 to 10 where 0 indicates ‘no pain’ and 10 indicates ‘worst pain imaginable’. Participants mark the level of pain that they feel in that moment for both arms. The VAS has been widely used and has shown to be a reliable and valid instrument for assessing pain.

The Brief Pain Inventory (BPI) short form [33-35]: This version of the BPI has the front and back body diagrams, four pain severity items (assessment the pain in its ‘worst’, ‘least’, ‘average’, and ‘now’) and seven pain interference items with daily activities whose scores range from 0 (no interference) to 10 (interferences completely). Pain severity and pain interference are obtained from mean scores. Furthermore the pain is answered in the last 24 h in this short form and there is an item about percentage of pain relief by treatment.

